#### Clinical Outcomes

To address research question 2a and hypothesis 2a, we will examine whether the Acceset training curriculum can enhance the 4 components of psychological well-being among befrienders and seekers. We will compare the change in mattering, selfhood, compassion, and mindfulness scores of befrienders between baseline and following Acceset training (ie, before vs after training) and those of seekers over the course of the study. As for research question 2b and hypothesis 2b, we hypothesized that engagement with Acceset digital peer support will lead to improved mental well-being of the seekers compared with the control group and that this effect may be sustained beyond the period of the intervention. To assess these effects, we will evaluate the change in mental well-being of the participants in both study groups (intervention and control) after 3, 6, and 9 weeks from baseline using self-report questionnaires. Seekers will provide responses pertaining to help-seeking behavior beyond the Acceset platform at weeks 6 and 9 using the perceived social support measure in the questionnaire battery. We will assess the correlations of the 3 digital features—comprising emotion and functional adjustment stickers and motivation GIFs, which reflect seekers’ mental well-being during engagement with the platform—with their well-being scores from the questionnaires.

The scale or set of scales used to assess the clinical outcomes, including the 4 components of psychological well-being underpinning the Acceset training curriculum, measures of seekers’ well-being, and perceived social support, are outlined in the following paragraph.

“Mattering” will be assessed via the Rosenberg Mattering Scale [52]. *Selfhood* comprises self-knowledge, interpersonal self, and self-agency and will be assessed via the following respective scales: the Rosenberg Global Self-Esteem Scale [53], the Self-Consciousness Scale [54], and the General Self-Efficacy and Social Self-Efficacy Scales [55]. *Compassion* will be assessed as operationalized in the Compassion Cultivation Training [56] comprising three stages: (1) an awareness of distress, (2) affective concern, and (3) a responsiveness or readiness to help relieve that distress (motivational). *Mindfulness* will be regarded as a flexible cognitive state in which individuals are actively present and notice novel aspects in both the environment and one’s perspectives [45]. We will evaluate the participants’ responses based on the degree to which they harness the approaches pertaining to the enhancement of mindful self-acceptance: (1) identifying novel aspects of the situation or perspective; (2) demonstrating “work in progress” by using possibility words such as “could be” and offering other interpretations of the situation their peers have shared; (3) highlighting puzzles and paradoxes in the peer-disclosed emotional experiences (eg, how their peers may feel victimized yet are responsible for being in that situation), which builds tolerance for ambiguity and decreases the experience of psychological symptoms; (4) noticing humorous aspects of the situation; (5) perceiving the situation from multiple perspectives; (6) considering alternative (useful) aspects of a problematic context or the silver lining; (7) emphasizing a mental file of positive memories; and (8) encouraging peers in mindfulness journaling. *Anxiety* will be measured using the Generalized Anxiety Disorder Questionnaire [57]. *Depression* will be measured using the PHQ-9 [38]. *Perceived social support* will be assessed using the Multidimensional Scale of Perceived Social Support [58].

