**Aims and hypotheses**
Aim 1: the first aim is to evaluate the implementation effectiveness of digital peer support training between emerging adults providing support (befrienders) and emerging adults seeking help (seekers).Research question 1a: is Acceset digital peer support training an effective training curriculum in providing peer support?Hypothesis 1a: the digital peer support training is effective for befrienders in providing peer support, as demonstrated by the adoption of and fidelity to the training curriculum.Research question 1b: is the Acceset text-based intervention (ie, the platform) feasible and acceptable (ie, safe and timely) as an ongoing mechanism of support for seekers and befrienders?Hypothesis 1b: digital peer support is feasible and acceptable in offering support for emerging adults’ mental well-being, which is evidenced by 2 indicators:The engagement of the seeker-befriender-moderator interaction across the 4 time points—baseline (before the intervention), 3 weeks (conclusion of the intervention), and 6 and 9 weeks (carryover effect assessment)—that is indexed by the waiting period for seekers to receive a response. Delays are defined as a >48-hour waiting period and will be categorized based on the following reasons: (1) technical factors (eg, the befriender is not able to log into the platform to respond in time) and (2) human factors (eg, the befriender drops out from the study, and no replacement is found in time). An acceptable response time is within 48 hours, and this is emphasized during Acceset digital peer support training for befrienders [37].The use of technical features of the Acceset platform that is measured by the seeker dropout rate at each stage of engagement with the Acceset platform, the number of visits on the study registration website, the number of participants who registered with Acceset, the average number of letters exchanged, and the average number of emotion and functional adjustment stickers and motivation graphic interface formats used [37].Research question 1c: is the Acceset text-based intervention (ie, the platform) feasible and acceptable (ie, safe and timely) as an ongoing mechanism of support that identifies individuals who are at an unacceptably high risk of mental health conditions?Hypothesis 1c: digital peer support is feasible and acceptable in offering support for emerging adults’ mental well-being by identifying individuals who are at an unacceptably high risk of mental health conditions related to depression and suicidality, which is measured before and during engagement based on 3 means—specifically, the Acceset algorithm detection of the content of the letters, the moderators’ vetting of the content of seekers’ letters, and the seekers’ self-report responses to the 9-item Patient Health Questionnaire [38] (refer to the Implementation Outcomes section for details [37]).Aim 2: the second aim is to elucidate whether Acceset digital peer support harnesses the 4 components of emerging adult mental health—mattering, selfhood, compassion, and mindfulness.Research question 2a: does Acceset digital peer support enhance the 4 components among seekers and befrienders?Hypothesis 2a: Acceset digital peer support (training) increases the 4 components among befrienders (before and after training) and seekers (over the course of the study across 4 time points).Research question 2b: is Acceset digital peer support effective in improving emerging adult mental well-being?Hypothesis 2b: digital peer support leads to significantly better mental well-being of seekers compared with the control group. This effect is sustained beyond the period of the intervention.Aim 3: the third aim is to investigate the mechanism of change in emerging adult mental well-being involving digital peer support (delivered by the Acceset platform).Research question 3: what is the mechanism explaining the change in emerging adult mental well-being involving digital peer support?Hypothesis 3: the initial level and rate of change (ie, growth factors) of befrienders’ web-based support positively predict the growth factors of seekers’ psychological well-being in accordance with latent growth curve modeling.

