The proficiency of befrienders in applying these digital support skills will be evaluated through simulation and homework activities in which they will apply these skills to simulated letters that are adapted from actual cases of peer seeker emotional disclosure on the Acceset platform. All assignments will be reviewed and given feedback on. At the end of the training, befrienders are expected to apply the 4 components to their assigned peers’ disclosed emotional experiences. All participants who complete the training will receive a training certificate and will be invited to take on live cases and be part of the study.

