### Implementation and Clinical Study Outcomes

All implementation and clinical outcomes will be measured via the engagement with Acceset over 4 time points using the aforementioned questionnaire battery [37]. In this section, we delineate the outcome measures that correspond to each hypothesis examined in this study.

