The following approaches will be used for data analysis and interpretation. Independent-sample 2-tailed *t* tests will compare the intervention and control groups. Bonferroni post hoc tests will control for multiple comparisons. For both the intervention and control groups, additional independent *t* tests will compare seekers who provided data across all 4 time points with those who dropped out from the study for different reasons to ascertain if the sample with data across all 4 time points and the sample with fewer data points bias our results. For instance, seekers may drop out when risk assessments identify them as having a high risk of depression and suicidality during the course of the study. There will also be instances when befrienders discontinue the letter writing because of the sensitive nature of the letter content that may cause distress and befrienders not being fully comfortable, and the system will inform the seekers and obtain their consent to end the letter thread instead of continuing the conversation with a new befriender. Second, each participant’s emotional experiences disclosed on Acceset will be extracted based on the definitions of the 4 components of psychological well-being. Latent Dirichlet allocation analyses in R (R Foundation for Statistical Computing) and content analysis will be used [37,60,61].

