## Discussion

### Principal Findings

This protocol delineates the design of an RCT to assess the implementation and clinical effectiveness of Acceset. To our knowledge, the proposed intervention is the first to incorporate and validate digital markers of psychological well-being, harness components of emerging adult mental well-being, and elucidate a mechanism of change involving digital peer support in mitigating emerging adults’ psychological symptomologies. We hypothesized the following: (1) the digital peer support training will be effective for befrienders in providing peer support, as demonstrated by the adoption of and fidelity to the training curriculum with significantly higher scores after training than before training on the 4 components of well-being (selfhood, mattering, compassion, and mindfulness); (2) the digital peer support intervention will be feasible and acceptable in offering support for emerging adults’ mental well-being through the engagement of seeker-befriender-moderator interaction over the Acceset platform throughout the course of the study (baseline [before the intervention], 3 weeks [the end of the intervention], and 6 and 9 weeks [to measure carryover effects]) and the use of the platform’s technical features; (3) the digital peer support intervention will be feasible and acceptable in offering support for emerging adults’ mental well-being by identifying individuals who are at an unacceptably high risk of mental health conditions related to depression and suicidality based on the Acceset algorithm, moderators’ vetting of the letter exchanges, and seekers’ self-report responses to the PHQ-9; (4) the digital peer support intervention will lead to significantly better mental well-being of seekers compared with the control group, with the effect sustained beyond the period of the intervention; and (5) the mechanism of change, as indexed by LCM, will reveal that the initial level and rate of change (ie, growth factors) of befrienders’ web-based support positively predict the growth factors of seekers’ psychological well-being.

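### Hypothesis 2a names no comparator for the four well-being components, so a within-group rise from ordinary drift could be credited to Acceset

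*Protocol article*

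**What the plan says.** **Hypothesis 2a.** Textbox 1 of the protocol article states that Acceset "increases the 4 components among befrienders (before and after training) and seekers (over the course of the study across 4 time points"). Clinical Outcomes gives the matching assessment: the change in befrienders' component scores from before to after training "and those of seekers over the course of the study". Neither place mentions the wait-list arm.

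**Hypothesis 2b.** The next sentences of Clinical Outcomes name the comparator: mental well-being is to be evaluated in "the participants in both study groups (intervention and control) after 3, 6, and 9 weeks from baseline".

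**General analysis text.** Data Collection, Management, and Analyses says that independent-sample t "tests will compare the intervention and control groups", with Bonferroni control. It ties neither to a particular outcome or hypothesis.

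**Schedule.** Participants and Study Setting gives the battery to seekers and befrienders at baseline and at weeks 3, 6 and 9. Implementation and Clinical Study Outcomes adds: "All implementation and clinical outcomes will be measured via the engagement with Acceset over 4 time points using the aforementioned questionnaire battery".

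**Training.** Under Digital Peer Support Training, those who complete the course "will be invited to take on live cases and be part of the study". Principal Findings then describes the training hypothesis (1a) as shown by adoption and fidelity "with significantly higher scores after training than before training on the 4 components of well-being".

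**The concern.** Aim 2 asks whether Acceset itself strengthens the four components, which is a causal question. Scores can move over nine weeks of a semester for other reasons: term timing, repeated completion of the same questionnaires, and regression to the mean. A change within one group cannot be separated from these. For seekers, a randomised comparison that removes them already exists, but 2a as worded does not call for it.

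Befrienders are not randomised and have no control group. The article promises scores before and after training, but the stated schedule does not show where either falls. Principal Findings then makes those scores part of the evidence that the training works. At stake is a claim that Acceset or its training raised the components when the data show only that scores rose.

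**Working it through.** **1. Is a comparator named?** The article says that its outcomes section sets out the measures for each hypothesis, so the hypothesis-specific text matters.

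| | Groups named | Contrast |
|---|---|---|
| 2a, seekers | seekers | change over the study |
| 2a, befrienders | befrienders | before versus after training |
| 2b | intervention and control | change at weeks 3, 6 and 9, against control |

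Only 2b names a contrast between arms.

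**2. Where do the befriender scores fall?** The schedule has one point before the intervention and none between the end of training and the first live letter.
- If baseline precedes training, the next scheduled score (week 3) follows training plus three weeks of letters.
- If baseline follows training, which the order of events under Digital Peer Support Training allows, there is no pre-training score.

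On the visible schedule, neither placement isolates training.

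**3. Size of the risk, as an illustration.** The plan gives no figure for 2a to reproduce and names no within-group test. I take a paired t test as the natural test of change over time.

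Inputs from the article: 50 seekers per arm; 30 befrienders planned and 35 recruited; two-sided 0.05. Assumed: zero true effect, an upward drift of d SD common to both arms, and a baseline to follow-up correlation r of 0.5 to 0.7.

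The SD of change is √(2(1−r)), so the standardised change is dz = d/√(2(1−r)). The noncentrality is dz·√n on n−1 degrees of freedom.

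For n = 50 and d = 0.2:
- r = 0.5: dz = 0.2/1.000 = 0.200; noncentrality 0.200 × 7.071 = 1.41; rejection probability 0.284.
- r = 0.7: dz = 0.2/0.775 = 0.258; noncentrality 0.258 × 7.071 = 1.82; rejection probability 0.433.

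| Drift | Seekers, n = 50 | Befrienders, n = 30 | Befrienders, n = 35 |
|---|---|---|---|
| 0 | 5% | 5% | 5% |
| 0.1 SD | 11–15% | 8–11% | 9–12% |
| 0.2 SD | 28–43% | 19–28% | 21–32% |
| 0.3 SD | 55–77% | 36–54% | 41–61% |

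With Bonferroni over four components (0.05/4 = 0.0125), 0.2 SD drift and n = 50 give 13% to 23% per component.

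**4. The same drift with the wait-list arm used.** In 20,000 simulated trials at r = 0.5, with 50 per arm and no effect, a t test of change between arms rejected in 5.1% at 0.2 SD drift and 4.8% at 0.3 SD. The paired test in one arm rejected in 28.5% and 54.6%, in line with the formula.

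**The case against.** **Seekers.** A reader might infer that the wait-list arm goes unused for the four components. The article does not establish that. Participants and Study Setting uses the word seekers for all 100 randomised participants, the t-test sentence is unrestricted, and the abstract lists the four components among the clinical outcomes. A between-arm comparison is therefore not excluded. What stands is that 2a does not ask for one, while 2b beside it does.

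**Befrienders.** A reader might infer that no post-training measurement exists. That is also too strong. Clinical Outcomes states such a score, and Figure 1 and Multimedia Appendix 3, which are not shown, may place it. What stands is that the visible schedule and the promised comparison do not fit together.

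**Magnitude.** The 28% to 43% is not the trial's error rate. It belongs to a test that the article never names, under assumed drift and correlation, and before the Bonferroni control that the article does plan. Only upward drift would be credited to Acceset, and the article gives no basis for a direction. Entry is capped at a PHQ-9 of 9, so regression to the mean need not favour the intervention.

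**Importance.** Hypothesis 2b, on effectiveness for mental well-being, is explicitly controlled. That limits the severity but does not settle 2a, which carries its own causal claim.

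**Conclusion.** The point holds in a limited form. Hypothesis 2a is framed as change over time without a comparator, and a within-group rise would satisfy it as written. For befrienders the comparison is uncontrolled, and its timing is not reconciled with the schedule. Principal Findings also adds score changes to hypothesis 1a, whereas Textbox 1 and Implementation Outcomes rest that hypothesis on adoption and fidelity, assessed from the letters.

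How often a false claim would follow depends on the assumed drift and correlation. The direction does not: any common upward drift raises the rejection rate of a within-group test above nominal and leaves the between-arm test near 5%. This should be fixed. It does not undermine the trial's controlled comparison for 2b.

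**What to change.** **Seekers.** State 2a as the arm 1 minus wait-list difference in each component at weeks 3, 6 and 9, preferably adjusted for the baseline score. The article specifies no baseline-adjusted model for 2b, so the adjustment has to be written in. Report within-arm change as descriptive. The article describes mindfulness as rated from participants' responses and names no questionnaire for it. If it is scored only from letters, and so is unavailable in the wait-list arm, report it descriptively.

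**Befrienders.** State when the before- and after-training scores were taken, and reconcile Clinical Outcomes and Principal Findings with the four-point schedule. Label the change as uncontrolled and do not claim that it isolates a training effect. Results says that data collection is complete, so an added questionnaire is no longer an option.

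**Hypothesis 1a.** Align Principal Findings with Textbox 1 and Implementation Outcomes, so that 1a is judged on adoption and fidelity from the letters.

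**Cost.** No new data are needed for components measured by questionnaire in both arms, and Results reports that analysis was still in progress. The between-arm test asks more of the sample. At two-sided 0.05 and 80% power, 50 per arm detects (1.960 + 0.842) × √(2/50) = 0.56 SD unadjusted. Adjusting for baseline multiplies this by about √(1−r²), giving roughly 0.49 SD at r = 0.5 and 0.40 SD at r = 0.7, which is a further reason to adjust. For befrienders and 1a, the cost is a weaker claim and consistent wording.

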**Methods:**

A total of 100 participants (aged 19-25 years) from the National University of Singapore will be recruited and randomized into 2 arms. In arm 1 (n=50), the seekers will use Acceset with befrienders (n=30) as well as moderators (n=30) for 3 weeks. Arm 2 comprises a wait-listed control group (n=50). A questionnaire battery will be used to monitor seekers and befrienders at 4 time points. These include baseline (before the intervention), 3 weeks (end of the intervention), and 6 and 9 weeks (carryover effect measurement). Implementation outcomes of the intervention will involve evaluation of the training curriculum with respect to adoption and fidelity as well as user acceptability of the Acceset platform and its feasibility for broader deployment. Clinical outcomes will include mattering, selfhood, compassion, mindfulness, perceived social support, and psychological well-being scores.

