### Participants and Study Setting

We plan to recruit 130 participants (100 seekers and 30 befrienders) at the National University of Singapore (NUS) to engage with the Acceset intervention in accordance with an Institutional Review Board–approved protocol. Participants will be recruited via the Research Participation program within the Department of Psychology at NUS, where students will be awarded credits as part of the introductory courses for psychology. During recruitment, inclusion and exclusion criteria screening will be conducted via self-reporting. Participants qualified for inclusion (seekers) will be randomized into 2 arms. The seekers (n=50), befrienders (n=30), and moderators (n=30) in arm 1 will use Acceset for 3 weeks. The control group (n=50) in arm 2 will be wait-listed for Acceset use. It should be noted that the wait-listing approach is a standardized approach for RCTs pertaining to digital mental health [37,39,40].

We will recruit age- and gender-matched individuals from NUS. The 4–time-point questionnaire battery of arm 1 will be used to compare the mental well-being and help-seeking behavior with those in arm 2 [37]. Moderators will be recruited from the Singapore Executive Counselling and Training Academy. If an unacceptably high risk of depression and suicidality is detected at any time point by the moderator, who is a certified counselor, they will reach out to the participant, who will be directed to different clinical mental health support providers, including counseling centers and hotlines, on the NUS campus. On the basis of power analysis and the finding that 20% to 40% of the emerging adults enrolled in an IHL typically experience distress, this sample will provide a sufficiently powered comparator group.

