**Figure 1 figure1:**
[figure not shown]
Diagrammatic flow in terms of sequence of events on the Acceset digital text-based intervention (ie, the platform). CSQ-8: Client Satisfaction Questionnaire-8; GAD-7: Generalized Anxiety Disorder-7; MPSS: Multidimensional Scale of Perceived Social Support; PHQ-9: 9-item Patient Health Questionnaire; RMS: Rosenberg Mattering Scale.

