#### Community Engagement

The essence of the Acceset intervention draws on emerging adult support within the Singapore ecosystem and community by tapping into the shared experiences among emerging adults and training them to harness the 4 components of psychological well-being to bolster each other’s mental well-being (Figure 2). Seekers can further the community efforts by joining as befrienders and being trained to provide web-based peer support. By engaging clinicians, psychologists, and counselors, the Acceset intervention emphasizes the availability of peer support that leverages the lived experiences of the community. The building of the seeker-befriender-moderator relationship also aims to deepen the authenticity of peer support rather than being a “transaction” for referral, as evidenced by the effective implementation of the intervention when seekers’ and befrienders’ satisfaction with the support system and sense of perceived social support relate positively to their psychological well-being.

In addition to a community-based structure for facilitating digital peer support, Acceset engages education stakeholders at various IHLs in the advice of safety standards and protocols for effective and compliant digital peer support that is in accordance with the ethics of members of the helping profession. Education stakeholders play an important role in normalizing a new service delivery model through various formal and informal outreach channels. This could entail mass mailing of a new service and organization of an information session where students can learn more about the new service and how participating in it can be beneficial for their mental well-being. Attending college can be a particularly stressful time, especially in Asian societies with a high cultural value ascribed to educational achievement and a high level of competition [49,50]. The experience of heightened psychological distress is a salient problem, with an average of 20% to 40% of students reporting distressed symptoms [50]. This finding, coupled with the increasing number of emerging adults enrolled in 2- or 4-year colleges (40% in 2013 to 70% in 2018) [51], provides the impetus for leveraging a community approach in the development of digital peer support that intervenes in emerging adults’ psychological well-being.

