With regard to user referral to appropriate mental health support providers, the seeker-befriender-moderator interaction will identify participants at an unacceptably high risk of depression and suicidality before and during engagement based on 3 means. First, the Acceset algorithm will scan the content of the letter exchanges for high negativity and suicidal thoughts and expressions. Second, moderators with the required background and assessment tools will identify seekers at risk by vetting all the letter exchanges for high negativity and suicidal thoughts and expressions. Third, seekers will self-report their responses to the PHQ-9, and those that meet the clinical cutoff scores (PHQ-9 >9) will be excluded at the start of the study. During the course of the study across the 4 time points, seekers with an unacceptably high risk of depression and suicidality (PHQ-9 >9) will be referred to an appropriate mental health care provider, including counseling centers and hotlines, on the NUS campus. Seekers’ self-reported responses to the PHQ-9 serve as the primary risk assessment to make referrals to appropriate mental health support providers.

At recruitment, we will assess the percentage of participants identified as being at an unacceptably high risk of depression and suicidality meeting the clinical cutoff of PHQ-9 >9 that has a sensitivity of 88% and specificity of 88% for major depression [38] and exclude them from the study. During the course of the study, we will ascertain the percentage of events when a befriender correctly alerts the moderator that the seeker is at an unacceptably high risk of depression and suicidality as confirmed by the moderator, who will vet every letter exchange. During the course of the study and for every letter exchange, we will tabulate the percentage of events when a moderator correctly identifies a seeker with an unacceptably high risk of depression and suicidality. Both the befrienders and moderators will use the PHQ-9 as a systematized coding structure to code seekers’ letter content to ensure generalizability and validity in risk assessment across both coders—befrienders and moderators. Finally, we will tabulate the percentage of events when a seeker who is at an unacceptably high risk of depression and suicidality (both during the recruitment process and during engagement with the platform) receives directions to an appropriate mental health care provider, including counseling centers and hotlines, on the NUS campus.

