
The study team will alert the counseling center on the NUS campus about the referrals of at-risk seekers to ensure that adequate and appropriate support is provided to them. In addition, at weeks 6 and 9, there will be a follow-up on all seekers (to measure carryover effects), which helps ensure the psychological safety of the seekers. At the start of the study, all seekers are provided with the participant informed consent and information sheet, which states that they will be referred to and their information shared with the NUS counseling center if their risk assessment across the 4 time points indicates an unacceptably high risk of depression and suicidality (PHQ-9 >9).

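### Help-seeking is to be compared between arms, but the only measure the text assigns to it is the perceived social support score, which by its name and its listing as a clinical outcome measures something else.

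*Protocol article*

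**What the plan says.** Four statements in the protocol article bear on this.

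- **The comparison.** Participants and Study Setting says that the four-time-point questionnaire battery of arm 1 "will be used to compare the mental well-being and help-seeking behavior with those in arm 2". Help-seeking stands beside well-being as a separate thing to compare.
- **How help-seeking is captured.** Clinical Outcomes says: "Seekers will provide responses pertaining to help-seeking behavior beyond the Acceset platform at weeks 6 and 9 using the perceived social support measure". No other sentence says how it is measured.
- **The instrument.** Later in Clinical Outcomes, perceived social support "will be assessed using the Multidimensional Scale of Perceived Social Support". The Figure 1 legend lists the same instrument ("MPSS: Multidimensional Scale of Perceived Social Support").
- **The status of the score.** The Methods part of the abstract says: "Clinical outcomes will include mattering, selfhood, compassion, mindfulness, perceived social support, and psychological well-being scores". Perceived social support is thus an outcome in its own right.

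**The concern.** Seeking help elsewhere is something a person does. Perceived support is how supported a person feels. The article plans to compare the first between arms and assigns it a measure of the second. This is not a detail left for another document to fill in, because the article does name a measure.

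The score is also an awkward stand-in in this particular trial. Acceset is a peer support intervention, so a rise in felt support in arm 1 is a result it is meant to produce. If the plan is followed as written, that benefit could be reported as more help sought outside the platform, with nothing in the text to separate the two.

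**Working it through.** No arithmetic applies. The documents give no help-seeking rate, no expected change in the support score and no relation between the two, so the check is a reading of the sections side by side.

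1. **Is a comparison between arms planned?** Yes. Participants and Study Setting names arm 2 as the comparator for help-seeking behavior.

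2. **Which measure is assigned?** Only the sentence in Clinical Outcomes answers this. It gives the perceived social support measure at weeks 6 and 9.

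3. **Does another named instrument fit?** The scale paragraph in Clinical Outcomes names eight scales if the two self-efficacy scales are counted separately: mattering, self-esteem, self-consciousness, general self-efficacy, social self-efficacy, anxiety, the PHQ-9 and perceived social support. Compassion and mindfulness are described there without a further named scale. The Figure 1 legend adds a client satisfaction questionnaire. None of these is, by name, a measure of help-seeking.

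4. **What could a difference in the score mean?**
   - Higher in arm 1: Acceset may have made participants feel more supported, with no change in outside help, or they may have sought more outside help and felt better supported for it.
   - Lower in arm 1: this does not show that less outside help was sought.
   - No difference: this does not show equal help-seeking, because a gain in felt support and a change in outside help could offset each other.

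   In each case the score leaves the help-seeking question open. Even the direction of the link is unknown, since people who seek help elsewhere may feel more supported or less.

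5. **What rests on it?** Help-seeking as an outcome is in none of the hypotheses in Textbox 1, is not among the clinical outcomes in the abstract, and is not mentioned in the analysis paragraphs of Data Collection, Management, and Analyses. It rests on one clause in Participants and Study Setting and one sentence in Clinical Outcomes.

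**The case against.** The strongest objection is that the content of the measure cannot be checked. No item of the scale is printed, and the battery is in Multimedia Appendix 3, which is not shown. Items on help-seeking may have been added to the support section at weeks 6 and 9, and the restriction to two of the four time points would fit that. This stands as a limit: a reader might infer that the trial collected nothing on help-seeking, and the documents do not support that. It does not rescue the sentence, which refers the reader to the support measure and to no separate item.

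A second objection is that the two sections may concern different things. Outside help in addition to the platform means little for wait-listed controls who do not yet have it, and hypothesis 2b uses the word seekers for the intervention arm alone. The Clinical Outcomes sentence might therefore describe a follow-up of platform users only. That is possible, although Participants and Study Setting calls all 100 randomized participants seekers. On this reading, the planned comparison between arms has no stated measure at all, so the text still needs correcting.

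A reader might also infer that the score serves as an implementation outcome as well. Community Engagement does say that effective implementation is shown when satisfaction and "sense of perceived social support relate positively to their psychological well-being". That describes an association with well-being. Implementation Outcomes does not list the score, and using one score in several analyses is no error in itself.

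Finally, a reader might look to referrals as a substitute, since the study tabulates how often an at-risk seeker "receives directions to an appropriate mental health care provider" and "The study team will alert the counseling center on the NUS campus about the referrals of at-risk seekers". Being referred is not the same as seeking help. In addition, algorithm scanning and moderator vetting work on letter exchanges, which the wait-listed arm does not have, so a comparison by arm would be empty for those routes.

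**Conclusion.** The point holds, and it is minor. The article assigns to help-seeking a measure that, by its name and its listing as a clinical outcome, is a measure of perceived support. An arm difference in that score cannot be read as help sought outside the platform.

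This rests on two things. The first is that the scale measures what its name and listing say, since its items are not shown. The second is that the Clinical Outcomes sentence supplies the measure for the planned comparison, as no other sentence does.

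No numerical size can be given, because any figure would consist wholly of assumptions. A reader might infer that the trial's main result is compromised. It is not: the well-being comparison uses other scales, and no hypothesis concerns help-seeking. What changes is one secondary statement that the trial should not make from this score.

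**What to change.** Report the Multidimensional Scale of Perceived Social Support only as perceived social support.

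Then check the battery in Multimedia Appendix 3:

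- If it holds a help-seeking item asked in identical form in both arms, correct the Clinical Outcomes sentence to name that item and its time points, and use it for the comparison in Participants and Study Setting.
- If it does not, delete help-seeking from that comparison and remove the Clinical Outcomes sentence.

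The Results section says data collection was completed in June 2022, so an item cannot be added now. The cost is a check of the existing questionnaire and a change of wording in two places, made before the results are reported.
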